### Strategies to Improve Adherence to Interventions

No group will be monitored regarding adherence, as the app is essentially self-guided. However, the app sends daily messages to participants to remind them to access the app and complete at least 1 activity.

### Outcomes

#### Primary Outcomes

Anxiety symptom is 1 of the 2 primary outcomes, and it will be measured by the Generalized Anxiety Disorder–7 Scale (GAD-7). It consists of 7 items that the person assesses on a scale of 0-3 according to the frequency with which each symptom has disturbed them during the past 2 weeks [23]. It shows high reliability in Chilean samples (Cronbach α=0.86 [24]).

Depression symptoms will be measured by the PHQ-9 depression scale, which consists of 9 items that evaluate the presence of depression symptoms present in the past 2 weeks, with a response scale of 0=never, 1=some days, 2=more than half the days, and 3=almost every day. With a Cronbach α of 0.83, its reliability is high in Chilean samples [25]. Additionally, depression and anxiety symptoms in the past week will be assessed through the Patient Health Questionnaire–4 (PHQ-4) [26].

Primary and secondary outcomes will be assessed at 3 time points: preintervention (baseline), immediately post intervention (30 days post intervention), and 1-month follow-up in all groups.

#### Secondary Outcomes

##### Well-Being

Perceived psychological and overall well-being is measured by the Pemberton Happiness Index scale (PHI), a 21-item instrument evaluated in 2 subscales: psychological well-being (experienced 5 positive and 5 negative experiences) and subjective well-being (remembered). The scale is Likert-type, with scores per item from 0 to 10 [27].

##### Resilience

Perceived resilience is measured by the Brief Resilience Scale (BRS), a 6-item instrument on a Likert scale from 1 to 5. It has 3 inverted items, and the rating results from the average of the scores obtained [28].

##### Ruminative Thoughts

Rumination and ruminative thoughts are assessed by the Ruminative Response Scale (RRS, short version), consisting of 10 items that measure ruminant thoughts in 2 dimensions: reflection and restlessness. It has a high level of internal consistency (Cronbach α=0.85). Each item is scored on a 4-point Likert scale from 1 (almost never) to 4 (almost always) [29].

##### Emotional Regulation

Emotional regulation is assessed by the Emotional Regulation Questionnaire (ERQ), a 10-item questionnaire designed to measure respondents’ tendency to regulate their emotions in 2 ways: (1) cognitive reappraisal (1, 3, 5, 7, 8, and 10) and (2) expressive suppression (2, 4, 6, and 9) [30].

##### Mindfulness Skills

Mindfulness skills are assessed with the Mindfulness Attention Awareness Scale (MAAS), an instrument composed of 14 items on a Likert scale from 1 to 6. The scores obtained are added, and the higher the score, the greater the ability to pay attention fully and consciously. The average scores of the nonclinical participants are 65 points out of a total of 84 [31].

### Participant Timeline

See Table 1 for the participant timeline.

**Table 1 table1:** Participant timeline.

Time point			2023												2024																
			Enrollment							Allocation					Post allocation											Close-up					
			September		October		November		December			January		February			March		April		May		June		July			August	September		October
**Enrollment**																															
	Contact with health centers and prospects	✓		✓																											
	Eligibility screen			✓		✓		✓																							
	Allocation							✓			✓																				
	Informed consent										✓		✓																		
**Interventions**																															
	Intervention all arms															✓															
**Assessment**																															
	Baseline variables												✓																		
	Outcome variables															✓		✓		✓											
**Dissemination**																															
	Analyses																					✓		✓			✓				
	Results presentation and publication																												✓	✓	

### Sample Size

To achieve the aims of the study, we have considered 4 arms. To obtain a statistical power of 0.80, a minimum sample size of 36 participants is required for each of the 4 arms. Controlling for a dropout rate of 26%, as shown by the literature on behavioral experiments linked to mobile apps for symptoms related to mood and anxiety [32,33], a final sample size of 49 participants per group is required. The sample size approximation was made based on the literature on statistical power and sample sizes in clinical and social science research [34], while the estimate to reduce the effects of the percentage of abandonment in the experimental conditions was calculated based on Wang and Ji [33]. Thus, an estimate of 196 participants sufficiently obeys such parameters. In addition to the quantitative data collection, a qualitative collection of information will be carried out through focus groups. Regarding the number of focus groups, a total of 4 have been established, 1 for each study group. The size of the focus groups, following the recommendations in the literature [35], is estimated at a total of 32 participants (reaching an estimate of the saturation point), that is, 8 participants per focus group.

### Recruitment

The strategies for achieving adequate participant enrollment to reach the target sample size will include contacting and presenting the study to municipality authorities, who are expected to help establish contact with public health authorities. Interested individuals can sign up to participate through the QR code available in pamphlets delivered to primary health clinics in the Maule area. Health staff in the selected public clinics will also encourage patients to participate in the study.

### Assignment of Interventions: Allocation

#### Sequence Generation

Participants will be randomly assigned to any group with a 1:1 allocation through a website. The web system will generate randomization based on the rand() function of the PHP language. Through this function, a random number between 0 and 3 is generated and subsequently assigned to the participants upon recruitment.

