## Methods

### Study Setting

Participants will be adults (18 years of age and older) in the Maule Region of Chile and mixed-sex. We expect to recruit 49 participants per arm, configuring 196 participants in total.

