### Recruitment and Informed Consent

For recruitment, invitations will be made through the social networks of the Center for Applied Psychology and the Faculty of Psychology of the University of Talca. In addition, the educational and health services of 4 districts in the region will be contacted to disseminate the multiplatform application Cuidandome to adults. The call for participation will include an explanatory video and an informed consent form, which will be available on and collected through the project website (under development). Participants will be recruited through convenience sampling and will be randomly assigned to 1 of the 4 groups by means of simple randomization (through the PHP: Hypertext Preprocessor rand() function).

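### Simple randomisation by independent rand() draws gives the required 49 per arm only on average; a permuted-block list in the same web system would hold every arm at or close to 49 at almost no cost

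*Protocol article*

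**What the plan says.** The allocation method appears in three places in the protocol article, and they agree. Recruitment and Informed Consent says that people are assigned "by means of simple randomization (through the PHP: Hypertext Preprocessor rand() function". Sequence Generation and Allocation Implementation both describe the draw: "a random number between 0 and 3 is generated and subsequently assigned to the participants upon recruitment". Both also state the ratio as 1:1, although there are four arms: "Participants will be randomly assigned to any group with a 1:1 allocation through a website". No blocking, stratification, minimisation or cap on arm size is described.

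The target is in Sample Size: "To obtain a statistical power of 0.80, a minimum sample size of 36 participants is required for each of the 4 arms". The article then allows for 26% dropout and concludes that "a final sample size of 49 participants per group is required". Study Setting repeats the number more softly: "We expect to recruit 49 participants per arm, configuring 196 participants in total".

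Statistical Methods for Primary and Secondary Outcomes adjusts every model for sex, age, education and concurrent psychological or psychiatric treatment. The Discussion lists the effect of simultaneous psychotherapy on the primary outcomes as a difficulty.

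**The concern.** The sample size is set per arm, but the mechanism controls only the total. Independent draws with probability 1/4 make the arm sizes multinomial. Once 196 people are in, some arm will almost always be short of 49, and nothing in the plan corrects this.

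The single control arm makes it matter more. The hypothesis in Aims sets each strategy arm against monitoring and psychoeducation alone, so one arm enters all three contrasts. If that arm comes out small, the three lose precision together. Chance imbalance on concurrent treatment, a covariate that the plan itself treats as important, is likewise left unrestricted at allocation.

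**Working it through.** **Inputs from the protocol article.** Power 0.80, 36 evaluable per arm, 26% dropout, 49 randomised per arm (Sample Size); total 196 (Study Setting); independent draws over four values (Sequence Generation), taken as probability 1/4 each.

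**1. The plan's own figure.** 36 / (1 − 0.26) = 36 / 0.74 = 48.65, rounded up to 49; 4 × 49 = 196. This reproduces. The 36 itself cannot be reproduced, because the article gives no effect size, significance level or sidedness.

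**2. Arm sizes under simple randomisation.** Each arm is Binomial(196, 1/4):
- mean = 196 × 0.25 = 49
- SD = √(196 × 0.25 × 0.75) = √36.75 = 6.06
- central 95% range 37 to 61.

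Jointly the arms are Multinomial(196; 1/4, 1/4, 1/4, 1/4). The probability of exactly 49 in all four is 196! / (49!)⁴ / 4¹⁹⁶ = 0.04%. Simulation (1,000,000 draws) gives:

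| Quantity | Result |
|---|---|
| Mean smallest arm | 41.9 |
| 5th percentile of smallest arm | 36 |
| P(smallest arm below 45) | 77% |
| P(smallest arm below 40) | 22% |
| P(smallest arm below 36, before any dropout) | 4.4% |
| Mean gap, largest minus smallest | 14.4 |

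An arm of 42 leaves about 42 × 0.74 = 31 completers. Under simple randomisation, about 256 people would have to be randomised for a 95% chance that every arm reaches 49.

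**3. Power (assumption needed).** Assume a pairwise two-sided 5% normal test. Then 36 per arm at 80% power implies d = (1.960 + 0.842) × √(2/36) = 0.66. Power for completer counts a and b is Φ(0.66 / √(1/a + 1/b) − 1.960). With dropout random at 26%:

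| | Simple randomisation | 49 fixed per arm |
|---|---|---|
| One pairwise contrast, mean | 79.4% | 80.0% |
| One pairwise contrast, 5th percentile | 72.6% | 75.8% |
| Weakest of three control contrasts, mean | 76.5% | 78.5% |
| P(some arm has fewer than 36 completers) | 97% | 86% |

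The mean losses are 80.0 − 79.4 = 0.6 points and 78.5 − 76.5 = 2.0 points.

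**4. Arm sizes under blocking, 196 randomised.**
- One unstratified list in blocks of 4: exactly 49 in each arm, since 196 = 49 × 4.
- Random blocks of 4 and 8 in two strata: every arm exactly 49 in about 27% of runs; mean smallest arm 48.2; lowest seen 46, largest seen 52. These results hardly change whether 20%, 30% or 50% of participants are assumed to be in the smaller stratum.

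**The case against.** The strongest reply is that nothing here is an error. Simple randomisation is openly specified, unbiased and unpredictable, and needs no list to protect. Study Setting speaks of an expected 49 per arm, and Sample Size presents 196 as an estimate, so 49 can be read as a planning figure that the method meets on average. This stands. A reader might infer that the article contradicts itself or that the randomisation is unsound; the documents support neither.

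It can also be said that the effect is small. The probability that some arm falls below 49 exceeds 99.9%, but that is close to automatic, since any departure from a perfect split triggers it. The mean power loss is 0.6 points for one contrast, less than the uncertainty in the dropout figure. On the plan's own minimum of 36 completers, blocking moves the risk of a short arm only from 97% to 86%, because random dropout dominates. A lower cut-off would show a larger gain, but the plan states no such cut-off. This too stands, and it limits the claim to one of efficiency.

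Two further inferences should be resisted. One is that stratified blocking would deliver exactly 49; it usually does not, because the last block in a stratum may be incomplete. The other is that imbalance on concurrent treatment is likely. The article gives no prevalence for it, and every model already adjusts for it, so such imbalance is possible and partly mitigated.

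What survives is that the plan calls 49 per group required and uses a mechanism that leaves the smallest arm at about 42 on average, when a near-free alternative exists.

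**Conclusion.** The point holds as a cheap improvement in balance and precision; it does not make the trial invalid. The arm-size results rest only on the stated 196 and independent equal-probability draws. They show a typical shortfall of about 7 in the smallest arm (49 − 42) and a smallest arm below 40 in roughly one trial in five.

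The power figures rest on more: an assumed d of 0.66, a two-sided 5% pairwise test, completers only, and dropout at 26% independent of arm. They would change with a different effect size or with the planned repeated-measures model. On those assumptions the loss is about 0.6 points for one contrast and about 2 points for the weakest control contrast. A reader should not conclude that the trial is materially underpowered because of its randomisation, nor that blocking secures 36 completers in each arm.

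**What to change.** Before recruitment opens, replace the rand() draw with a pre-generated permuted-block list held on the server and concealed from the study team. Use randomly varying blocks of 4 and 8, and write the ratio as 1:1:1:1 in both allocation sections. Amend the wording on simple randomisation in Recruitment and Informed Consent to match.

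Stratification by concurrent psychological or psychiatric treatment (yes/no) is optional. It is self-reported at eligibility and is already a model covariate, so the analysis need not change. If exact equality matters more than balance on treatment or unpredictability, a single unstratified list in fixed blocks of 4 gives exactly 49 per arm at 196.

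The cost is a small code change and one stored list; the article says that the trial is not yet recruiting. There are two modest downsides: the list must be kept concealed, including from anyone in contact with participants, and allocation becomes slightly more predictable. Random block sizes and automatic web allocation limit the second.

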#### Concealment Mechanism

After the randomization and allocation, participants will not receive information regarding the group they belong to. Instead, they will be instructed to access the app and complete the emotional regulation activities, regardless of the type. The participants will only have access to a version of the app that includes the strategies that correspond with their assigned group. Additionally, this information will not be disclosed to the assessment research team (outcome evaluators) to keep the participant allocation blind.

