### Aims

The main aim of this study is to develop a multiplatform self-help mental health mobile app for adults and to test the effectiveness of its assessment, psychoeducation, and emotional regulation strategy modules post intervention and at 1-month follow-up. We hypothesize that the combination of psychoeducation and any self-regulatory strategies will prove more effective than the evaluation and psychoeducation components alone in decreasing symptomatology.

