### Trial Design

This is a protocol for a double-blind, 4-armed randomized controlled trial (ClinicalTrials.gov NCT05997849) evaluating changes in primary and secondary outcomes (symptomatology and well-being variables) post intervention and at follow-up. The 4 arms will be group 1 (control): the participants will have access only to the monitoring and psychoeducation module for 30 days; group 2: participants will have access to the monitoring module, psychoeducation, and mindfulness strategies for 30 days; group 3: participants will have access to the monitoring module, psychoeducation, and behavioral activation strategies for 30 days; and group 4: participants will have access to the monitoring, psychoeducation, and cognitive strategies module for 30 days. Additionally, 1 focus group per condition will be carried out to qualitatively assess the user experience with the app and its overall usability.

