### Interventions

#### Description of Interventions

Cuidandome is a multiplatform self-help mental health app that does not constitute a psychological treatment. The mobile app will be available for iOS and Android operating systems, and it is composed of 3 modules: monitoring, psychoeducation, and strategies for people to learn to manage their emotional states and their depression or anxiety symptoms.

The modules of the app are given below.

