### Assignment of Interventions: Blinding

#### Who Will Be Blinded?

This is a double-blinded trial, blinded to the participants and the research team. A data analyst will work with the final data set, where the group condition will be masked.

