### Data Collection and Management

#### Plans for Assessment and Collection of Outcomes

Self-report questionnaires assessing primary and secondary outcomes will be administered at baseline (immediately before intervention), post intervention, and follow-up. Primary outcomes will be assessed through the website and the app, and secondary outcomes will be measured only on the website.

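### The masking instruction asks every participant for activities that the control app does not contain, so participant blinding is not secured for the strategy-versus-control contrasts

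*Protocol article*

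**What the plan says.** All references are to the protocol article.

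- **How allocation is hidden** (Concealment Mechanism). Participants are not told their group. In place of that information, "they will be instructed to access the app and complete the emotional regulation activities, regardless of the type". The same section adds: "The participants will only have access to a version of the app that includes the strategies that correspond with their assigned group".
- **What the control arm has** (Trial Design). For group 1, "the participants will have access only to the monitoring and psychoeducation module for 30 days". Groups 2, 3 and 4 have the same two components plus mindfulness, behavioral activation or cognitive strategies respectively.
- **Where the regulation content sits** (Description of Interventions). Of the app: "it is composed of 3 modules: monitoring, psychoeducation, and strategies for people to learn to manage their emotional states". The Regulation Strategies (RS) Module section describes this third module on its own and divides it into the three strategy types.
- **The blinding claim** (Who Will Be Blinded?). "This is a double-blinded trial, blinded to the participants and the research team".
- **The hypothesis** (Aims). It is expected that "the combination of psychoeducation and any self-regulatory strategies will prove more effective than the evaluation and psychoeducation components alone".
- **The outcomes** (Plans for Assessment and Collection of Outcomes). Participants supply the scores themselves: "Self-report questionnaires assessing primary and secondary outcomes will be administered at baseline (immediately before intervention), post intervention, and follow-up".

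**The concern.** The instruction is the masking device itself. Its closing words, on type, suit a participant who has one of three kinds of strategy. They do not suit a participant who has none. A control participant is asked for something the app does not offer, and the request is itself a cue that something has been withheld.

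At stake is the comparison the trial was set up to make. GAD-7 and PHQ-9 are filled in by the participant, who is in effect the outcome assessor. Keeping the evaluators and the analyst unaware of the arm, which the plan does, cannot protect a score that the participant supplies. If some controls work out that they have a reduced version, their expectations and their reporting may change in that arm alone, while the published report would still describe participants as blinded.

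**Working it through.** The point is a comparison of statements, with a little arithmetic to show its reach.

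**Step 1. Number affected.** The Sample Size section asks for 36 per arm and allows for 26% dropout. 36 / (1 − 0.26) = 36 / 0.74 = 48.6, rounded up to 49; 4 × 49 = 196. The plan's figures reproduce. The control arm is expected to hold 49 / 196 = 25% of participants. Simple randomization is used, so the actual number will vary around 49.

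**Step 2. Can the instruction be followed in each arm?**

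| Group | Monitoring | Psychoeducation | Regulation strategies | Instruction can be followed |
|---|---|---|---|---|
| 1 (control) | yes | yes | none | no |
| 2 | yes | yes | mindfulness | yes |
| 3 | yes | yes | behavioral activation | yes |
| 4 | yes | yes | cognitive | yes |

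The rows come from Trial Design. The separation of the strategies from the other two modules comes from Description of Interventions and the Regulation Strategies (RS) Module section.

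**Step 3. Which contrasts are exposed?** Four arms give 4 × 3 / 2 = 6 pairwise contrasts. Three of them involve group 1, and these are the ones named in the hypothesis. A shift in the control arm's reported mean enters all three with the same sign, because they share that arm. The other three, between strategy arms, do not contain group 1 and are untouched.

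**Step 4. Does another feature of the plan remove the problem?**

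- Masking of the evaluators and the analyst stays intact, but the outcomes are self-reported.
- Baseline is measured before the intervention starts. A participant can find that activities are absent only after opening the app, so analysing change from baseline does not remove the effect.
- The model covariates (sex, age, educational level, concurrent treatment) do not measure awareness of the arm.
- The article describes no sham or matched activity in group 1 and no separate wording for that arm.

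**Step 5. Size.** The documents give no figure for how many controls would notice or how far their scores would move, so no bias estimate is offered.

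**The case against.** The strongest reply is that the text shows a mismatch, not an unmasking. Concealment Mechanism summarises the approach and is not the script that participants read. A control user sees one version and has nothing to compare it with. To be unmasked, that user must notice an absence, suppose that other versions differ, and conclude that theirs is the control. The control app is not empty either: it has daily mood ratings, weekly assessments and psychoeducation, and some users could take these for the activities meant. This stands, and it is why the point is put as blinding not secured rather than blinding lost. It does not remove the mismatch: as written, the instruction names a kind of activity that group 1 lacks.

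A reader might go further in four ways that the documents do not support.

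- *The control arm is revealed.* That is a plausible inference. The promise of extensive information at recruitment does not settle it, because the article does not say that arm content is disclosed.
- *The bias must favour the strategies.* Lower expectation would act that way. But a control participant who senses missing content might seek help elsewhere, which would act the other way, and dropout could rise in either kind of arm.
- *The focus groups also break the blind.* The plan says "1 focus group per condition will be carried out to qualitatively assess the user experience" but does not say when or by whom. A condensed article may leave that to the full protocol, and nothing places the groups before follow-up or has outcome evaluators running them.
- *The daily reminder and the consent text share the fault.* As reported, the reminder asks only for one activity, without naming a kind, and could be met in any arm. The consent text is not shown.

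**Conclusion.** The concern holds in a limited form. The masking instruction, the content of the control arm and the statement that participants are blinded do not fit together. The instruction cannot be followed by about a quarter of participants and may show them that content is missing. Participant blinding is therefore not secured for the three contrasts that test the main hypothesis, all on self-reported outcomes. It may hold among the three strategy arms, and evaluator and analyst masking is not in question.

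The conclusion rests on the instruction reaching participants in substantially the form the article reports, and on control content being as Trial Design states. The mismatch can be read directly from the text. That controls would notice, and how far their scores would then shift, is inference.

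**What to change.** 1. Replace the instruction in Concealment Mechanism, and wherever it is given to participants, with wording that is true in all four arms, for example: *use the app daily and complete the content it offers*.
2. Align Trial Design and Who Will Be Blinded? with what the design delivers: evaluators and analyst masked, participants not told their arm, participant blinding partial.
3. Add one item at post-intervention, placed after the outcome questionnaires, asking which version the participant thinks they had, with a don't-know option. Report the answers by arm. Guesses can also reflect perceived benefit, so the item describes unmasking and should not be used to adjust the comparison.

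The article says that recruitment has not begun, so the changes can be in place for every participant. The cost is a text edit, one extra web item and a softer blinding label. The item might also prompt some participants to think about their version before the 1-month follow-up, which is a small price for having data on the question. Treatments, sample size and analysis model do not change.
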